**Implementation**																	
	Feasibility	Implementation drivers (barriers and facilitators)		Qualitative focus group discussions guided by the CFIR												✓	
	Fidelity	The proportion of participants who read the messages at least once a day		Survey questionnaire						✓		✓		✓		✓	
	Cost	Comparative cost of developing and maintaining both strategies		STEM metadata		✓		✓		✓		✓		✓		✓	

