### Randomization and Blinding

We will use computer-generated block randomization to ensure balance (1:1) between the two treatment groups. Randomization codes will be provided via text message directly to the blinded researcher’s password-protected phone line with a secure online backup. This will occur for enrollment as each participant signs the consent form. All study participants will complete baseline assessments before randomization, and follow-up assessments will occur through online surveys with the survey links delivered via text messaging or email messaging depending on which study arm participants belong to. Participants will be asked to use either the email address or phone number with which they receive messages as their study ID on the follow-up online surveys.

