**Reach**																	
	Dose delivered	The frequency of emails and text messages sent to the subscribers (including delivery failures)		STEM metadata		✓		✓		✓		✓		✓		✓	
	Dose received	The average number of times participants read the emails or text messages		Survey questionnaire						✓		✓		✓		✓	

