#### Data Collection

Participants who provide informed written consent and agree to participate in the study will be asked to complete a baseline assessment questionnaire that captures both demographic and clinical information. At 6, 12, and 24 weeks, an online survey link will be sent to participants via email or text messages along with an invitation for them to complete the assessments. Participants will enter the email address or phone number through which they receive the messages as their study identifier at the start of the survey so that their data at the 4 time points can be matched. Participants who have not completed their follow-up assessments within 3 days of the due date will be contacted by a research coordinator and reminded to do so, or if they require assistance to complete the assessment, such assistance will be offered, including the option to complete the assessment over the telephone. In instances where such assistance is required, a blinded research assistant will be asked to read out the survey questions to the participant and record their responses.

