#### Data Collection

Quantitative data will be collected on the implementation outcomes: acceptability, fidelity (adherence to reading messages), and sustainability (continued utilization). Data will be collected using user satisfaction survey questionnaires at 6, 12, and 24 weeks for the two study arms.

Qualitative data will be collected via focus group (see details below) discussions involving the patients. The discussion topic guide will be informed by the CFIR domains and will also elicit participants’ views on barriers and facilitators to the implementation of both strategies.

We will invite a random sample of 10 participants via text message and email to take part in a virtual focus group workshop using end-to-end encrypted teleconferencing (with appropriate consent for confidentiality) to discuss the impacts of the interventions. In order to explore the reasons why participants remain or drop out of the study, we will hold a focus group for a cross-section of participants who remained in the study and those who dropped out to discuss the impacts of the supportive email and text message interventions. Thus, an invitation will go to both those who remain in the study and those who dropped out, and participation in the focus group workshop will be voluntary. We will offer a CAD $50 (US $39) gift card as honorarium to cover the cost for participants attending the focus group.

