##### Addressing Missing Data

Though preventing missing data is difficult in clinical research, measures will be put in place by the researchers to minimize the occurrence of missing data. This includes having a well-defined data collection strategy that is understood by all study personnel, as well as having a simple set of questionnaires to collect only relevant data needed, minimizing the number of follow-ups with participants, and creating substantial gaps in the number of follow-ups. The investigators will identify and actively engage the participants who would be at the greatest risk of being lost during follow-up. Further, the data collection would be monitored and reported in as close to real time as possible during the study. Notwithstanding the above, the mean substitution strategy would be employed by the research team to handle missing data [48]. Here, the mean value of a variable is used in the place of the missing data value for that same variable. This allows the researchers to utilize the collected data in an incomplete data set. Questionnaires with more than 20% missing responses will be excluded.

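### Fidelity and dose received rest on survey responders, and neither missing-data rule counts a participant who stopped reading as a non-reader

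*Protocol article*

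**What the plan says.** All references are to the protocol article.

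- **Measures and source.** Table 1 defines fidelity as "The proportion of participants who read the messages at least once a day" and dose received as "The average number of times participants read the emails or text messages". Both list a survey questionnaire as their only source. The STEM metadata in the same table cover messages sent, delivery failures, subscriptions and cost, but not reading.
- **Timing.** Implementation Evaluation, Data Collection: "Data will be collected using user satisfaction survey questionnaires at 6, 12, and 24 weeks for the two study arms".
- **Route of the survey.** Randomization and Blinding has follow-up done online, "with the survey links delivered via text messaging or email messaging depending on which study arm participants belong to".
- **Follow-up of non-completers.** Effectiveness Evaluation, Data Collection: "Participants who have not completed their follow-up assessments within 3 days of the due date will be contacted by a research coordinator". Help is then offered, with completion by telephone as an option.
- **Missing data.** Addressing Missing Data, which stands under the Data Analysis heading of the Implementation Evaluation, adopts mean substitution: "the mean value of a variable is used in the place of the missing data value for that same variable". The same section excludes any questionnaire with more than 20% of its responses missing.
- **Purpose.** Study Aims and Objectives lists the comparison of the two strategies on fidelity and reach, among other implementation outcomes, as the first objective.

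**The concern.** Whether someone answers a survey about reading is probably related to whether they read. A participant who no longer opens the text or email channel is less likely to see a survey link that arrives there. The missing answers are therefore plausibly concentrated among those with low reading, which is the group the fidelity measure exists to detect.

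The stated rules do not allow for this. One fills the gap with the mean, the other drops the form, and neither lets a silent participant count as not reading. Table 1 speaks of participants, but the figure obtained describes responders. Fidelity and dose received could then be overstated in both arms. If one channel is ignored more than the other, the difference that the implementation comparison is meant to find could be masked. Exposure by arm also matters for reading the noninferiority result, since similar symptom scores mean little if it is unclear how much of each intervention was received.

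**Working it through.** **Inputs from the protocol article.** 50 randomised per arm; projected maximal overall dropout 20%; 80 evaluable patients (Sample Size).

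**Assumptions.** The article gives neither survey response by arm nor the reading rate among responders. I take p = 0.80 of responders reading daily, and vary p from 0.60 to 0.90 and non-response from 10% to 40%.

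**Step 1: the plan's own figure.** 80 / (1 − 0.20) = 100, or 50 per arm. This reproduces. At that loss, 0.80 × 50 = 40 per arm answer.

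**Step 2: three treatments of the 10 silent participants in one arm.**
- Excluded: 32/40 = 80%.
- Filled with the arm's mean: (32 + 10 × 0.80)/50 = 40/50 = 80%.
- Counted as not reading daily: 32/50 = 64%.

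The first two agree at any response rate, because adding values equal to the mean cannot move the mean. This takes the mean within arm, which the section does not specify. A mean pooled over both arms would pull each arm's figure towards the other and would still not count anyone as a non-reader.

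**Step 3: range.** The distance between the responders' figure and the lower bound is p × non-response. The smallest case is 0.60 × 0.10 = 6 points, the largest 0.90 × 0.40 = 36 points.

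**Step 4: precision.** Among responders, SE = √(0.80 × 0.20 / 40) = 0.063. After filling, the sum of squares stays at 40 × 0.16 = 6.4 while n rises to 50, so the naive SE = √(6.4 / 49 / 50) = 0.051. The ratio is about 0.81. Filling adds no information but shortens the interval; exclusion does not have this effect.

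**Step 5: comparison between arms, with p = 0.80 among responders in both.**

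| Assumed non-response, text v email | Difference, excluded or filled | Difference, non-responders counted as not reading |
|---|---|---|
| 20% v 20% | 0 | 64% − 64% = 0 |
| 15% v 25% | 0 | 68% − 60% = 8 points |
| 10% v 30% | 0 | 72% − 56% = 16 points |

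With equal non-response and equal reading among non-responders, the comparison is not distorted; only the level in each arm is.

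**The case against.** The strongest points on the other side are these.

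1. **Non-responders are not clearly mean-filled.** A reader might infer from the mean-substitution sentence that every silent participant is given the average. The text does not support that as a certainty. An unreturned questionnaire is wholly missing and, read literally, falls under the 20% exclusion rule, so filling would reach only returned forms with few gaps. The section does not say outright which rule covers an unreturned form. This objection stands against the loss of precision in Step 4, which needs filling. It does not touch the point estimate, which is the same either way.

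2. **The survey does not reach people only through the evaluated channel.** Coordinator contact after 3 days and telephone completion are planned, and eligibility requires both a phone and an email address. This stands, and it should reduce non-response. It does not remove it: the protocol still allows for 20% loss. These provisions are written for the follow-up assessments, and the article does not state that they cover the user satisfaction survey.

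3. **Continued use is not survey-only.** Although Implementation Evaluation, Data Collection groups "fidelity (adherence to reading messages), and sustainability (continued utilization" together, Table 1 also takes sustainability from dropout and subscription data. A reader might infer that continued use is overstated in the same way, but a non-survey source is planned, so the point is confined to fidelity and dose received. Dropout by arm would show part of any difference. It would not show a participant who stays subscribed and stops reading.

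4. **The gap between arms is assumed.** This stands. The 8 and 16 points follow directly from the response rates put in, and would be real only if no non-responder reads daily. Some people skip questionnaires and still read a short message.

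5. **Counting non-responders as non-readers is an equally untestable extreme.** This also stands. If one arm merely answers surveys less, that count would create a false difference. It serves as a bound and should not be the sole main analysis.

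**Conclusion.** The point holds in limited form. Fidelity and dose received are self-reported by those who answer, and both stated missing-data rules return the responders' estimate. Participants who stopped reading and stopped answering are thereby counted as average readers.

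At the protocol's 20% loss, with an assumed 80% of responders reading daily, the plan would report 80% against a lower bound of 64%. Over the assumed ranges the distance is 6 to 36 points. These are bounds on what could be hidden, not estimates of bias. The understated standard error (0.051 instead of 0.063) arises only if unreturned forms are filled.

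The article does not establish that a difference between email and text is being concealed. That requires non-response, or reading among non-responders, to differ by arm, and the article gives no figure for either. What it does establish is that the analysis as stated could not reveal such a difference if it existed.

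**What to change.** - State that mean substitution is not applied to fidelity or dose received.
- For each arm and time point, report two figures: the responders-only figure, and the figure with all randomised participants as denominator and non-responders counted as not reading.
- Beside them, give survey response by arm, with the delivery-failure and subscription data already being collected.
- Conclude that email and text differ, or do not differ, in fidelity only if the conclusion holds across both figures.
- State whether the coordinator reminder and telephone option cover the user satisfaction survey, and which missing-data rule governs a questionnaire that is never returned.

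This needs no new data collection. It costs one extra table and a few sentences. The downside is a wider and less favourable range for fidelity, and possibly no firm conclusion on the difference between arms if response is low or uneven.

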**Maintenance**																	
	Sustainability	Dropout rates; barriers and facilitators		Subscription data; qualitative focus group discussions guided by the CFIR												✓	

^a^RE-AIM: Reach, Effectiveness, Adoption, Implementation, and Maintenance.

^b^CFIR: Consolidated Framework for Implementation Research.

### Effectiveness Evaluation

#### Hypothesis

As the same messages will be delivered through the supportive text message program and the email program, we hypothesize that daily email messaging will not be inferior to daily supportive text messaging in reducing depression symptoms and improving quality of life for patients with MDD. We further hypothesize that participant dropout rates and satisfaction rates will be comparable in the two arms of the study.

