### Sample Size

Based on the effect sizes (Cohen *d* of 0.85 and 0.67) achieved in 2 previous randomized trials (n<80 for each trial), which compared daily supportive text messages plus treatment as usual with treatment as usual alone for the management of patients with MDD, a sample size of 80 is estimated to have sufficient power for the current protocol. Allowing for a projected maximal 20% overall dropout rate, we propose to recruit 100 patients with MDD into the trial, with 50 patients randomly allocated into each study arm.

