#### Outcome Measures

The primary effectiveness outcome measures for the study will be the differences between mean scores on the following scales measured at baseline, 6, 12, and 24 weeks for the two study arms: the PHQ-9, WHO-5, and GAD-7.

The PHQ-9 scale will be used to provide depression symptom scores [35]. The PHQ-9 is a 9-item validated instrument (associated with a Cronbach alpha of .89) that is used to diagnose and measure the severity of depression in general medical and mental health settings. Each of the 9 questionnaire items is scored between 0 (not at all) to 3 (nearly every day). Higher scores on the scale indicate higher levels of depression. The PHQ-9 demonstrated good convergent validity with related constructs with an adequate internal consistency [45].

The WHO-5 will be used to measure patients’ quality of life [46]. The WHO-5 is a short 5-item questionnaire that measures the subjective well-being of the respondents. The scale has adequate validity as an outcome measure in clinical trials and as a generic scale for assessing well-being over time or between groups [47].

Secondary outcomes include changed mean scores on the GAD-7 scale [37] at baseline, 6, 12, and 24 weeks for the two study arms, as well as participant dropout rates and satisfaction rates at 12 and 24 weeks in the two arms. The GAD-7 is a validated 7-item questionnaire (associated with a Cronbach alpha of .92) that is used to assess the self-reported levels of anxiety in respondents in the 2 weeks prior to assessment. Each item on the scale is scored between 0 (not at all) to 4 (nearly every day). Higher scores on the scale indicate higher levels of anxiety.

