#### Data Analyses

We will summarize the baseline demographic and clinical characteristics of participants in raw values and percentages and compare them between the two treatment arms using chi-square or Fisher exact tests and appropriate *t* tests. The primary and secondary outcome measures will be analyzed using descriptive and inferential statistical analysis. For the primary outcome measures, we will use analysis of covariance (ANCOVA) to assess the change in scores between the two treatment arms, with baseline PHQ-9 and WHO-5 scores as covariates; the treatment arm as the independent variable; and PHQ-9 and WHO-5 scores at 6, 12, and 24 months as respective dependent variables for each time point. Secondary quantitative outcome measures will be compared using chi-square or Fisher exact tests and appropriate *t* tests.

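### Dropout and satisfaction are hypothesized to be comparable, but the only planned analyses are tests of difference, which cannot support that conclusion

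*Protocol article*

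**What the plan says.** Apart from the noninferiority hypothesis for depression symptoms and quality of life, the protocol article's Hypothesis section adds: "We further hypothesize that participant dropout rates and satisfaction rates will be comparable in the two arms of the study". No tolerable difference is attached to it.

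The Outcome Measures section lists these among the secondary outcomes: "participant dropout rates and satisfaction rates at 12 and 24 weeks in the two arms".

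The Data Analyses section fixes how they are analysed: "Secondary quantitative outcome measures will be compared using chi-square or Fisher exact tests". The same sentence also names t tests. It gives no confidence-interval criterion, equivalence test or noninferiority test for them.

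The Sample Size section rests on symptom-score effect sizes for text messaging against usual care. It states that "a sample size of 80 is estimated to have sufficient power for the current protocol" and then inflates for attrition: "Allowing for a projected maximal 20% overall dropout rate, we propose to recruit 100 patients with MDD into the trial". The allocation is equal, so each arm has 50. The section makes no precision or power statement for dropout or satisfaction.

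**The concern.** Comparability is a claim that the arms differ by no more than some tolerable amount. Chi-square, Fisher and t tests ask the opposite question: whether there is evidence of any difference at all. A significant result would contradict the hypothesis. A non-significant one leaves it undecided, because in a trial of this size non-significance is likely even when the arms differ materially.

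This is separate from the analysis of PHQ-9 and WHO-5 by ANCOVA. The hypothesis, outcomes and tests are different, and adding a noninferiority margin to the ANCOVA would not touch it.

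User satisfaction and feasibility are in the stated objective, and dropout is the quantitative measure of sustainability in Table 1. The Discussion says that the findings will inform a planned multicenter trial. If a non-significant test were taken as comparability, a real retention or satisfaction problem with email could be carried into that trial unnoticed.

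**Working it through.** **Inputs from the protocol (Sample Size).** 80 evaluable, 100 recruited, 50 per arm, and a maximum of 20% dropout overall. The plan's own figure reproduces: 80 / (1 − 0.20) = 100, which is 50 randomized and 40 completers per arm.

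**Assumed inputs.** The protocol names no important difference; 15 percentage points is used as an illustration. Dropout rates were chosen so that the two-arm average stays within 20%. The text-arm satisfaction rate is set at 83%, borrowed from the Text4Mood result in the Introduction. That result concerns perceived improvement in well-being in another program, so it is only a stand-in. Dropout is counted over all 50 randomized per arm, and satisfaction over 40 completers per arm.

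**Chance that the planned test misses a true 15-point disadvantage of email.** With X and Y independent binomials of size n and rates p₁ and p₂, sum P(X=i)·P(Y=j) over all tables (i, j) whose two-sided p-value exceeds 0.05. Chi-square is uncorrected.

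| Outcome | n per arm | Text v email | Overall rate | Missed, chi-square | Missed, Fisher |
|---|---|---|---|---|---|
| Dropout | 50 | 12.5% v 27.5% | 20% | 52% | 62% |
| Dropout | 50 | 10% v 25% | 17.5% | 47% | 59% |
| Dropout | 50 | 5% v 20% | 12.5% | 34% | 49% |
| Satisfaction | 40 | 83% v 68% | 75.5% | 65.4% | 73.5% |

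A scenario of 20% v 35% dropout gives 61% and 68%, but its overall rate is (20 + 35)/2 = 27.5%, above the protocol's stated maximum. It is therefore not used for the conclusion.

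**Precision.** The approximate half-width of the 95% confidence interval for a difference, at equal true rates, is 1.96·√(2p(1−p)/n):
- dropout, p = 0.20, n = 50: 1.96·√(0.32/50) = 1.96 × 0.080 = 15.7 points;
- satisfaction, p = 0.83, n = 40: 1.96·√(0.2822/40) = 1.96 × 0.084 = 16.5 points.

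**Could comparability be shown at this size?** With truly equal rates (20% dropout; 83% satisfaction), the probability that the whole Newcombe 95% interval lies within ±15 points is about 3% for dropout and 1% for satisfaction. Within ±20 points it is about 41% and 32%. Changing the test alone would therefore not make a comparability claim likely.

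**The case against.** **A reader might infer that the trial will most likely report email as comparable even when it is 15 points worse.** The protocol does not support this. It nowhere says that a p-value above 0.05 will be read as comparability, and it promises descriptive as well as inferential analysis, so observed rates may stand beside the p-value. Two outcomes are also tested. If email were 15 points worse on both, and the outcomes were independent, then using 12.5% v 27.5% for dropout, the chance that neither is significant at one time point is about 0.52 × 0.65 = 34% (chi-square) or 0.62 × 0.735 = 46% (Fisher).

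**A reader might also put the miss rate at 60% to 75% for both outcomes.** For dropout that needs rates above the protocol's 20% overall maximum or a denominator of 40 rather than 50 per arm. Only satisfaction reaches that range, and then under a borrowed 83% rate.

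**Other points on this side.** The outcomes are secondary and no power is claimed for them. Focus groups also inform sustainability. Satisfaction may be scored and compared by t test. The choice of interval method or margin could properly be left to an analysis plan. These points limit the severity. They do not remove the mismatch: a t test is also a test of difference, and the article has itself chosen a type of test that cannot support its own stated hypothesis.

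**Conclusion.** The point holds as a mismatch between a stated hypothesis and its stated analysis. It does not rest on missing detail, and nothing else in the article repairs it.

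The practical size is moderate. Under an assumed 15-point gap, the planned tests would miss an excess of dropout with email in roughly one third to three fifths of trials, and a deficit in satisfaction in roughly two thirds to three quarters. These figures depend on the assumed gap and base rates, the number analysed and the choice of chi-square or Fisher. The logical point depends on none of them.

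Because the outcomes are secondary, this should be corrected but does not threaten the primary analysis.

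**What to change.** In Data Analyses, make the analysis of dropout and satisfaction the risk difference (email minus text) with its 95% confidence interval, for example by Newcombe's method, at 12 and 24 weeks. Use the mean difference with its interval if satisfaction is scored. State that a non-significant difference will not be reported as comparable.

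In Hypothesis, restate the sentence as estimation of the difference in dropout and satisfaction rates, with an expected 95% confidence interval half-width of about 16 percentage points. Alternatively, keep the word comparable but allow it only if the whole interval lies within a margin fixed before the data are seen.

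The cost is a change of wording in two sections and a few lines of analysis code, with no extra patients or data. The downside is that the trial will probably be unable to claim comparable dropout or satisfaction, and will offer only an estimate with a wide interval.
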